Firstly, we will create multiple subsets from the non-AF dataset (ranging from 500 to 5000 patients, in 500-patient increments) and train our ML models on these subsets. Performance will be evaluated using a fixed test set (25% of the non-AF dataset, *n* = 1952). Learning curves will be plotted to depict performance against training subset size, which will help visualise the point at which performance stabilises, indicating diminishing returns with additional data. If this stabilisation point aligns with the size of the AF dataset training set (*n* = 2072), we will be reassured that our sample size is likely adequate. The similarity between the non-AF and AF datasets, which will have at this stage been assessed via descriptive statistics, will inform the reliability of this inference. Learning curves specific to the AF dataset will be generated to further assess the legitimacy of this inference. This will employ the same process, training ML models on progressively larger subsets of the AF dataset (ranging from 500 to 2000 patients, in 500-patient increments) before plotting performance against training subset size. Importantly, DL models will use an enhanced sample size via transfer learning, leveraging 7809 non-AF patients during pretraining. This strategy is beneficial because it addresses the power law that has been observed for large neural networks, whereby performance improves according to *y* = *x*^a^, with *a* < 0 [89], implying that as the number of training samples (*x*) increases, the generalisation error (*y*) decreases at a slowing rate.

KL divergence will be used to assess the generalisation capability of both ML and DL models by comparing the predictive distributions between training and test subsets of the AF dataset. A small KL divergence will suggest that the training and test sets are similarly representative of the underlying distribution, corroborating that the sample size is adequate. The following rule of thumb will guide our judgement: if KL divergence < 0.01, the two distributions will be deemed almost indistinguishable; values between 0.01 and 0.1 will imply minor differences, and >0.1 will indicate more substantial differences [90].

Post hoc analyses of (observed) power are admittedly substandard. However, the insights gained from these methods will offer valuable insight into our dataset’s sufficiency given the absence of specific guidance at the time of writing [86].

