##### Secondary Analysis

DL will be used to leverage the non-AF cohort data. A transfer learning strategy will be adopted: the MLP (a multilayered feed-forward neural network) will be pretrained on the non-AF dataset, and the best-performing pretrained model will be transferred to the AF dataset for fine-tuning. In other words, the model will initially learn from the larger dataset and then refine its parameters downstream on the target dataset, enhancing its predictive performance for the latter. This technique exploits the layer-wise modular architecture of neural networks, that is, the fact a network can be constructed by removing all layers after a particular layer and appending a new connected layer with a different configuration of neurons and initial weights. As a result, the MLP will have learnt from 10,572 AIS patients, all the while prioritising the 2763 with AF. Indeed, the pretraining paradigm has become dominant because it has enabled the use of neural networks in small datasets, where it would not be cautious to train models from scratch [108]. Generally, the more similarity between the datasets, the more benefits conferred by transfer learning, including higher asymptotic accuracy, enhanced generalisability, and accelerated convergence. We consider our situation well-suited to this technique: the features of CHA_2_DS_2_-VASc are known to increase risk of AIS in patients without AF [40,71] and CHA_2_DS_2_-VASc does not incorporate AF-related parameters that impact AIS risk, such as duration of AF and left atrium/left atrial appendage (LAA) size, function, and morphology [101]. It has even been reported that CHA_2_DS_2_-VASc may be equally discriminative in the absence of AF [40].

Of course, no preprocessing parameters or summary statistics will be carried over from the non-AF to AF datasets. Pretraining (including its internal validation) will use only non-AF data, and during AF model development, all preprocessing will be fit within AF training folds only, with the AF hold-out test set untouched until final evaluation.

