##### MLP

MLP will be instantiated with default hyperparameters (i.e., optimizer = Adam(learning_rate = 0.01), loss = ‘binary_crossentropy’, metrics = [‘AUC’]), units = 32, hidden_layers = 2, activation = ‘relu’, kernel_regularizer = l2(0.01), dropout = 0.2 for the pretrained model; and the best hyperparameters found during pretraining for the fine-tuned model, with the exception of learning_rate = 0.00001).

Unlike the AF dataset, the non-AF dataset will not undergo random splitting. Rather, the MLP will be trained, hyperparameter-tuned, and retrained on the whole non-AF dataset to yield the so-called pretrained model. As above, 5 × 2 nested CV will be implemented and the best hyperparameters will be used to retrain the model on all non-AF patients.

The pretrained model will then be evaluated (AUC, F1 score, precision, sensitivity, specificity) and its last layer(s) will be removed, which are expected to be the more task-specific ones (i.e., non-AF patient-centric). These layers will be replaced by new, naive layers that culminate in an output layer with two neurons, given that we are performing probabilistic binary classification. The resulting neural network will be trained on ***T***, the training set of the AF dataset. Two strategies will be tried: fine-tuning of all layers, including pretrained ones (albeit with very low learning rates), and freezing of pretrained layers, with training confined to the newly added layers. In either case, the training phase will again employ 5 × 2 CV and the fine-tuned model will be retrained on ***T*** as a last step. Early stopping will be implemented with a patience parameter of 10 epochs, monitored on the validation loss during training.

Training performance will be reported using AUC, F1 score, accuracy, precision, sensitivity, and specificity. AUC, F1 score, accuracy, precision, and sensitivity will be used to inform whether the purely fine-tuned or the frozen model will be retained for evaluation on ***t***.

For reproducibility, matched random seeds will be set and reported across LR, XGBoost, and MLP models.

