NB will be plotted on the *y*-axis against risk threshold on the *x*-axis to yield a decision curve for each CPR. These curves, including the one for CHA_2_DS_2_-VASc, will be presented in a single figure to facilitate comparison. Additionally, we will plot lines representing the default strategies of ‘treat all’ and ‘treat none’, corresponding to scenarios where all or no patients are assumed to suffer 90-day recurrence, respectively. Incidentally, these lines will intersect at the observed prevalence of 90-day recurrence in our test set. A CPR will be considered clinically useful at a given risk threshold only if its NB exceeds that of both default strategies. Conversely, if a CPR’s NB is lower than either default strategy, it will be deemed clinically harmful. Our initial analysis will focus on determining whether the CPRs have higher NBs than the default strategies across the selected risk thresholds. We will then proceed to comparing the CPRs, ranking them based on descending NB, and identifying the three CPRs with the highest clinical utility (Table 3 and Table 4).

If an augmented CPR ranks among the three highest, we will perform test tradeoff analysis to compare it with the closest-ranking non-augmented CPR. The test tradeoff, calculated as Δ*NB*, represents the minimum number of additional tests per true positive required to justify the augmented CPR’s use, considering its added cost [124]. Of course, in our case, cost is not financial, but the additional time and reduced convenience associated with augmented CPRs, which include accompanying rules and are thereby more unwieldy than their non-augmented counterparts. If the NB differences across thresholds are small, the test tradeoff will be large, suggesting that the simpler CPR may be better, all things considered. After all, CHA_2_DS_2_-VASc owes its widespread adoption to its parsimonious, back-of-the-envelope nature. For clarity, we will report test tradeoffs in terms of both true positives and true negatives. The same approach will be applied to CPRs developed using MLP, where the test tradeoff will help decide whether the increased NB justifies the involvement of a less interpretable model. Ultimately, the purpose of reporting test tradeoffs will be to highlight which CPRs—if any—would be conveniently deployable without sacrificing significant clinical utility, and *not* to dismiss higher cost CPRs from future consideration.

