Primary: Does the acute context of AFAIS, and the importance of the index event, call for a CPR bespoke to early secondary prevention? In other words, are the main effects of the constituent features of CHA_2_DS_2_-VASc different post-stroke? Besides main effects, are there synergistic or other non-linear interaction effects between stroke history and the constituent features of CHA_2_DS_2_-VASc that can further improve prediction of 90-day AFAIS recurrence? Secondary: How do CPRs trained to capture 90-day AFAIS recurrence perform with regard to secondary outcomes (7-day recurrence, 7- and 90-day HT, 90-day decline in functional status, and 90-day all-cause mortality)? Exploratory: How do CPRs trained to capture 90-day AFAIS recurrence perform with regard to recurrence among non-AF AIS patients?	Primary: LR and XGBoost can capture the main effects of the constituent features of CHA_2_DS_2_-VASc in the context of secondary prevention. XGBoost is also equipped to capture complex functional relationships between the features. The outputs of these models can be employed to construct CPRs that outperform CHA_2_DS_2_-VASc for predicting 90-day recurrence in AFAIS patients. Specifically, fair (AUC < 0.8) to good (< 0.9) discrimination can be achieved for this high-risk group, alongside improved calibration and clinical utility relative to CHA_2_DS_2_-VASc. Secondary: The resulting CPRs also outperform CHA_2_DS_2_-VASc for predicting secondary outcomes.	LR and XGBoost models: Discrimination assessed using AUC and calibration curves. Calibration assessed using calibration curves, slopes, and Brier scores. Additional metrics: F1 score, accuracy, precision, sensitivity, specificity, Youden index, PPV, NPR, PLR, NLR. Resulting CPRs: Discrimination assessed using AUC and calibration curves. Calibration assessed using calibration curves, slopes, and Brier scores. Clinical utility assessed via DCA relative to default strategies as well as CHA_2_DS_2_-VASc. Test tradeoff analysis will be used to balance ease-of-use with clinical utility.	Primary: LR—680 patients deemed necessary, see Appendix S5.3 in Supplementary Materials file S3. XGBoost—learning curve analysis and KL divergence will afford post hoc insight on suitability of sample size. 75% of AF dataset will be used, comprising 2072 AFAIS patients. Remaining 25% (691 patients) will be withheld as test set. Secondary: Entire AF dataset will be used, comprising 2763 AFAIS patients. Exploratory: Entire non-AF dataset will be used as supplementary test set, comprising 7809 AIS patients.	Models will be instantiated (LR with L2 regularisation and XGBoost with default hyperparameters) on AF dataset, randomly split into training (***T***, 75%) and test sets (***t***, 25%), preserving distribution of outcomes. Nested cross-validation (5 × 2) will be employed for training and hyperparameter tuning. After hyperparameters are optimised, final models will be retrained using the entire training set. The test set ***t*** will then be used for evaluation of final LR and XGBoost models, focusing on discrimination and calibration. Feature importance will be reported via coefficients and odds ratios (ORs) for LR and feature gain for XGBoost. To derive CPRs from these models, SHAP will quantify both main effects and interaction effects of predictor variables. Main effects, represented by mean SHAP values, will be used to rank and assign scores to each predictor, enabling the creation of interpretable and clinically applicable CPRs. Interaction effects, captured through SHAP interaction values, will further refine our CPRs by identifying significant synergistic or redundant relationships between predictors. These interactions will be incorporated into so-called ‘augmented CPRs’ in the form of accompanying rules. Both non-augmented and augmented CPRs will be evaluated on the test set ***t*** in terms of discrimination, calibration, and clinical utility. Clinical utility will be measured using NB via DCA, plotting NB against risk thresholds within the 0.01–0.20 range. The CPRs will be compared on the basis of clinical utility to one another, CHA_2_DS_2_-VASc, and default strategies (‘treat all’ and ‘treat none’). Test tradeoff analysis will evaluate whether any incremental benefit in clinical utility observed with augmented CPRs justifies the added complexity of incorporating accompanying rules. Secondary: CPRs (and not models) will be evaluated on the entire AF dataset for each secondary outcome via discrimination, calibration, and clinical utility. Exploratory: CPRs (and not models) will be evaluated on the entire non-AF cohort to assess generalisability and compare their clinical utility when applied to an unseen yet closely related patient population.	Discrimination will be classified as follows [101]: AUC of 0.81–0.90 = good, 0.71–0.80 = fair, 0.61–0.70 = modest, and 0.51–0.60 = poor. Miscalibration is detrimental to medical decision making and poor calibration has been coined the Achilles heel for CPR applicability [102]. As such, we consider at least as important as discrimination and give precedence to clinical utility, which provides a more comprehensive evaluation by integrating both discrimination and calibration when interpreting the performance of our CPRs. CPRs will be considered clinically useful at a given risk threshold only if their NBs exceed those of both default strategies. Of those deemed useful, we will rank the CPRs (including CHA_2_DS_2_-VASc) based on NB across the 0.01–0.20 risk thresholds. Test tradeoff (∆*N**B*) will be interpreted only insofar as spotlighting those CPRs which would be more conveniently deployable without sacrificing significant clinical utility.

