
**Table 4 jcm-14-07327-t004:** Updating analyses; secondary.

Questions	Hypotheses	Outcome Measures	Sampling Plan (*N*, Power Analyses)	Analysis Plan	Interpretation Given to Different Outcomes
Primary: Does the acute context of AFAIS, and the importance of the index event, call for a CPR bespoke to early secondary prevention? In other words, are the main effects of the constituent features of CHA_2_DS_2_-VASc different post-stroke? Besides main effects, are there synergistic or other non-linear interaction effects between stroke history and the constituent features of CHA_2_DS_2_-VASc that can further improve prediction of 90-day AFAIS recurrence? Secondary: How do CPRs trained to capture 90-day AFAIS recurrence perform with regard to secondary outcomes (7-day recurrence, 7- and 90-day HT, 90-day decline in functional status, and 90-day all-cause mortality)?	Primary: MLP can capture the main effects of the constituent features of CHA_2_DS_2_-VASc in the context of secondary prevention, as well as complex functional relationships between stroke history and the other features. Its output can be employed to construct CPRs that outperform CHA_2_DS_2_-VASc for predicting 90-day recurrence in AFAIS patients. Specifically, fair (AUC <0.8) to good (<0.9) discrimination can be achieved for this high-risk group, alongside improved calibration and clinical utility relative to CHA_2_DS_2_-VASc. Secondary: The resulting CPRs also outperform CHA_2_DS_2_-VASc for predicting secondary outcomes.	See Table 3.	Learning curve analysis and KL divergence will afford post hoc insight on suitability of sample size. Data augmentation via transfer learning is particularly valuable for DL models like MLP, which are very data-hungry. Entire non-AF dataset will be used in pretraining phase, comprising 7809 AIS patients. 75% of AF dataset (***T***) will be used in fine-tuning phase, comprising 2072 AFAIS patients. Remaining 25% of AF dataset (***t***, 691 patients) will be withheld as test set.	The MLP model will leverage information within the non-AF patient dataset during pretraining. Non-AF AIS patients, who were not included in training the LR and XGBoost models—and therefore in no capacity informed the CPRs constructed thus far—may improve CPR generalisability and clinical utility. We contend our use case is well-suited to transfer learning given that the features of CHA_2_DS_2_-VASc are known to increase risk of AIS in patients without AF, and it has been reported to be equally predictive in the absence of AF [40]. MLP will be instantiated using default hyperparameters and undergo training, hyperparameter tuning, and retraining on the entire non-AF dataset to yield the pretrained model. The pretrained model will be evaluated (AUC, F1 score, precision, sensitivity, specificity) and its last layer(s) removed. These will be replaced by new, naive layers that culminate in an output layer with two neurons. The resulting neural network will be trained on the training set ***T***. Two strategies will be tried: fine-tuning and freezing. In either case, the training phase will again employ nested CV (5 × 2) and the fine-tuned model will be retrained on the AF training set. Training performance will be reported using AUC, F1 score, accuracy, precision, sensitivity, and specificity, used to inform whether the purely fine-tuned or the frozen model will be retained for evaluation on the test set ***t***. To derive CPRs from the MLP model’s output, SHAP will quantify main and interaction effects of predictor variables. Main effects, represented by mean SHAP values, will be used to rank and assign scores to each predictor. Interaction effects, captured through SHAP interaction values, will further refine our CPR by identifying significant synergistic or redundant relationships between predictors. These interactions will be incorporated into an ‘augmented CPR’ in the form of accompanying rules. Both non-augmented and augmented CPRs will be evaluated on the test set ***t*** in terms of discrimination, calibration, and clinical utility. The CPRs will be compared on the basis of clinical utility to one another, LR- and XGBoost-informed CPRs, CHA_2_DS_2_-VASc, and default strategies (‘treat all’ and ‘treat none’). Test tradeoff analysis will be performed. Secondary: CPRs (and not the MLP model) will be evaluated on the test set ***t*** for each secondary outcome via discrimination, calibration, and clinical utility.	See Table 3.

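### The MLP comparison changes model class and training data together, so a net-benefit difference from LR or XGBoost cannot be attributed to the network

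*Protocol article*

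**What the plan says.** Table 3 gives the training data for LR and XGBoost: "75% of AF dataset will be used, comprising 2072 AFAIS patients". It also gives the common test set ***t***: "Remaining 25% (691 patients) will be withheld as test set". Table 4 gives the MLP a further source: "Entire non-AF dataset will be used in pretraining phase, comprising 7809 AIS patients". It describes the non-AF patients as those "who were not included in training the LR and XGBoost models". Section 2.7 presents this as a gain in sample size: "DL models will use an enhanced sample size via transfer learning, leveraging 7809 non-AF patients during pretraining".

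The MLP subsection of Model Building plans two strategies: "fine-tuning of all layers, including pretrained ones (albeit with very low learning rates), and freezing of pretrained layers". Both start from the pretrained network.

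All CPRs are then ranked together on net benefit (NB) in ***t***. For the MLP-derived ones, the CPR Evaluation section says "the test tradeoff will help decide whether the increased NB justifies the involvement of a less interpretable model".

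**The concern.** The interpretability question is about model class: is a network worth its opacity compared with LR or trees? In the planned comparison two things differ at once, the model class and the patients it learned from. A higher NB for an MLP-derived CPR could come from the network, from the non-AF patients, or from both. A lower NB could be a weakness of the network or harm from pretraining on a cohort with different risk relations. The plan has no arm that holds one factor fixed while the other changes.

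A second statement also goes untested. Section 2.7 and the Secondary Analysis part of section 2.12.5 present pretraining as improving performance. Without an MLP trained on AF patients alone, the results can neither support nor contradict that.

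**Working it through.** **Patient counts.** The inputs are 2,763 AF and 7,809 non-AF patients (section 2.3) and a 75/25 split of the AF set.
- 0.75 × 2,763 = 2,072 for training and 2,763 − 2,072 = 691 for testing. Both match the plan.
- The Secondary Analysis part states "the MLP will have learnt from 10,572 AIS patients". 7,809 + 2,763 = 10,572 reproduces this, but the sum includes the 691 held-out patients. Patients used in MLP training number 7,809 + 2,072 = 9,881.
- 9,881 / 2,072 = 4.77, and 7,809 / 9,881 = 79% of the MLP's training patients are non-AF.

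**Planned arms.**

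| | AF data only | AF plus non-AF data |
|---|---|---|
| LR, XGBoost | planned | absent |
| MLP | absent | planned (fine-tuned or frozen) |

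Only one diagonal of the table is filled. The learning curves in section 2.7 do not fill the gap. Those built on non-AF subsets are scored on non-AF patients, and those built on AF subsets use no non-AF data.

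**How large could a data-only effect be?** The documents give no coefficients, so this is an illustration under assumptions: eight binary predictors, additive log-odds coefficients of 0.1 to 0.6, and a true AUC of about 0.61 to 0.62. The same ridge LR was fitted on 2,072 AF patients and on 2,072 + 7,809 pooled, with 150 replicates per setting. Non-AF coefficients either equalled the AF ones or differed from them by SD 0.3. NB is the mean over thresholds 0.05, 0.10, 0.15 and 0.20, and event rates follow the plan's range of 0.05 to 0.25.

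| Event rate | AUC, equal coefficients | NB change | AUC, SD 0.3 | NB change |
|---|---|---|---|---|
| 0.05 | 0.594 → 0.607 (+0.013) | +0.0005 | 0.605 → 0.599 (−0.006) | −0.0011 |
| 0.10 | 0.611 → 0.621 (+0.010) | +0.0009 | 0.611 → 0.600 (−0.011) | −0.0032 |
| 0.25 | 0.610 → 0.615 (+0.005) | +0.0006 | 0.610 → 0.596 (−0.014) | −0.0028 |

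**After conversion to point scores.** A separate illustration (300 replicates, additive truth, tiers ranked on LR coefficients) gave equal-slope gains in model AUC of 0.015 and 0.009 at event rates of 5% and 10%. The tiered scores gained only 0.006 and 0.004. With slopes differing by SD 0.3, the tiered scores changed by −0.001 and −0.005.

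**Against the noise in *t*.** SE² = [A(1−A) + (n₁−1)(Q₁−A²) + (n₀−1)(Q₂−A²)] / (n₁n₀), with Q₁ = A/(2−A) and Q₂ = 2A²/(1+A). At an event rate of 0.10, n₁ = 69.1, n₀ = 621.9 and A = 0.611, so SE = √[(0.238 + 4.53 + 55.95) / 42,973] = 0.038. At rates of 0.05 (35 events) and 0.25 (173 events) it is 0.052 and 0.026. These are errors of a single AUC. The error of a paired difference in the same ***t*** would normally be smaller, and the documents do not allow it to be computed.

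**The case against.** The plan is open about what the MLP is for. The Secondary Analysis part introduces deep learning as the means of using the non-AF cohort, and Table 4 says only that those patients may improve generalisability and utility. Read this way, the network and the extra data are one package, and comparing that package with CHA₂DS₂-VASc is valid. This stands, but it does not cover the interpretability judgement, which reads the package's gain as a return on model class.

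The test tradeoff is also advisory. The CPR Evaluation section and Table 3 say it highlights convenient CPRs and does not dismiss others. The MLP analysis is secondary. XGBoost against LR already shows the return on flexibility at fixed data, though not for a network. There are reasons for the missing arms too: the plan considers training a network from scratch on a small dataset incautious, and it keeps LR and XGBoost off the non-AF data so that they can be tested there. Neither reason rules out extra fits used only as comparators.

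A reader might infer that most MLP wins would be artefacts of the extra patients. In one simulation with equal slopes, the pretrained MLP beat AF-only LR on NB in 43% of replicates, against 5% for an AF-only MLP. Those rates do not carry over. They count wins of any size, score models rather than tiered point scores, use one threshold, omit class weights and dropout, and assume an additive truth that gives a network no structural advantage. The plan itself presumes interactions.

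**Conclusion.** The confounding of model class with training data is certain from the text. As planned, the interpretability judgement cannot separate the return on the network from the effect of 7,809 added patients, and the benefit of pretraining is asserted without a test.

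The documents do not support stronger conclusions: that the plan is biased toward the MLP, that it credits the network throughout, or that a CPR would be wrongly discarded. Under the stated assumptions, the data-only effect on model AUC is about +0.005 to +0.015 if coefficients match. It can be negative if they differ, is smaller in magnitude for point scores in the settings checked, and is small against the sampling error in ***t***. The primary LR and XGBoost analyses stand, as does the comparison of MLP-derived CPRs with CHA₂DS₂-VASc as a whole strategy. This is a cheap improvement to a secondary analysis.

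**What to change.** Add two fits as comparators only, using the same training set ***T***, folds and seeds:
1. The same MLP trained on ***T*** alone, tuned over the pretraining search space in Table 2, since the fine-tuning learning rates are meant for a network that has already been trained.
2. An LR that uses the non-AF data. For example, fit LR on the non-AF cohort, enter its linear predictor as a term in the AF model, and put the ridge penalty on deviations from it: logit p = α + γ(x′β_nonAF) + x′δ, with the penalty on δ. The model stays linear in the eight features, so the SHAP tiering applies unchanged.

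Convert both to CPRs by the planned SHAP procedure and score them on ***t***. In the CPR Evaluation section, base the interpretability judgement on data-matched pairs: pretrained MLP against LR with non-AF data, or AF-only MLP against AF-only LR. Judge the value of transfer on pretrained against AF-only MLP. If the fits are not added, describe any MLP gain as that of the MLP plus non-AF pretraining.

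Keep the AF-only LR and XGBoost for the non-AF evaluations. The cost is a little computation and a wording change. The LR that uses non-AF data cannot itself be evaluated on the non-AF cohort.

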The sample sizes derived from steps 1, 2, 3, and 4 were 288, 344, 680, and 459 patients, respectively. We therefore deemed a minimum total sample size of 680 patients necessary for CPR development. Given that our sample size is 2763 patients and the fact that we will perform validation and updating (and not development from scratch), we contend that our regression analyses are adequately powered. Of note, 75% of our dataset (*n* = 2072 patients) will be used for regression model training and the remaining 25% (*n* = 691 patients) will be reserved for testing. The fact our test set alone exceeds the required 680 patients further supports our sample size.

ML and DL techniques are inherently more data-intensive than regression [85]. This is because the number of predictors they consider far exceeds that of regression, even when the same set of predictors is considered, because they examine multiple interaction terms [84]. Unfortunately, guidance for a priori sample size calculations is currently lacking for most ML/DL techniques [86]. However, if closely related data are readily available, it has been suggested that inspecting model learning curves in the related dataset can be valuable to estimate the required sample size for the main dataset [87,88]. We will therefore explore the observed power of our non-regression models by means of learning curves on our non-AF dataset, as well as via a key information theoretic metric: Kullback–Leibler (KL) divergence.

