##### Model Building LR and XGBoost

We will instantiate LR with L2 regularisation and default hyperparameters (i.e., C = 1, max_iter = 100, solver = ‘lbfgs’), and XGBoost with default hyperparameters (i.e., n_estimators = 100, learning_rate = 0.1, max_depth = 3, objective = ‘binary:logistic’).

The AF dataset will be randomly split into two parts: training (***T***, 75%) and test sets (***t***, 25%), ensuring that the distribution of outcomes is preserved across both sets. LR and XGBoost models will each be trained, hyperparameter-tuned, and retrained on the training set (***T***), while the independent test set (***t***) will be withheld for final evaluation (Figure 1).

To achieve robust final models, we will employ nested cross-validation (CV) for training and hyperparameter tuning. Nested CV is particularly effective for small to moderately sized datasets because it promotes generalisability by ensuring that the hyperparameter tuning process does not contaminate the internal evaluation phase [113]. To this end, a 5 × 2 setup will be utilised, consisting of 5-fold CV in the outer loop and 2-fold CV in the inner loop (Figure 2). The set ***T*** will first be split into five equal parts. In each fold of the outer loop, one part (20% of ***T***) will serve as the intra-model test set ***T_t_*** while the remaining 80% will serve as the intra-model training set ***T_T_***. Each outer loop iteration will be subjected to an inner loop that further splits ***T_T_*** into two equal parts, using one as the true training set ***T_T_train_*** and the other as the validation set ***T_T_val_***, and alternating them over the two folds. The primary selection metric in the inner CV will be log loss (binary cross-entropy), with ties broken by calibration performance (Brier score).

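### At the planned 2072/691 split, the KL-divergence check in 2.7 says nothing about generalisation or sample-size adequacy

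*Protocol article*

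**What the plan says.** Section 2.7 notes that a priori sample-size guidance is lacking for most ML and DL methods. It therefore plans two later checks: learning curves and KL divergence. KL is meant to assess how well both the ML and the DL models generalise, by "comparing the predictive distributions between training and test subsets of the AF dataset". A small value is read as showing that the two sets are "similarly representative of the underlying distribution, corroborating that the sample size is adequate". Three descriptive bands follow: "if KL divergence < 0.01, the two distributions will be deemed almost indistinguishable", 0.01 to 0.1 means minor differences, and above 0.1 means more substantial ones. No KL estimator or binning is given.

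The sampling-plan cell of Table 3 says of XGBoost that "learning curve analysis and KL divergence will afford post hoc insight on suitability of sample size". Table 4 repeats this for the MLP. Under Model Building, the 75/25 split is random, "ensuring that the distribution of outcomes is preserved across both sets".

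**The concern.** A check on generalisation has to compare what a model predicts with what happened in patients it has not seen. This one compares predictions with predictions. One fixed model scored on two random parts of one cohort gives two risk distributions that differ only by sampling error, whether the model is good, useless or overfitted.

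The inputs make this sharper. Under CPR Development there are eight predictors: five comorbid items, sex and two age indicators. That is six binary features and a three-level age category, so at most 3 × 2^6 = 192 patterns. Any model, the MLP included, assigns one risk to each pattern. The training and test distributions can then differ only in how often each pattern occurs, and the random split keeps those frequencies close.

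At stake is one of the two supports named in Tables 3 and 4 for the sample size of XGBoost and the MLP. A reader could take a small KL as evidence that 2072 training patients suffice, when it carries no such information.

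**Working it through.** **Inputs from the article.** The cohort is 2763 ("Given that our sample size is 2763 patients"). 2763 × 0.75 = 2072.25 and 2763 × 0.25 = 690.75, which agrees with 2072 and 691 ("Remaining 25% (691 patients) will be withheld as test set"). The anticipated event rate is 0.05 to 0.25. XGBoost settings are the stated default (100 trees, rate 0.1, depth 3) and the most complex corner of Table 2 (200 trees, rate 0.2, depth 9). The article states no operating characteristic for the KL rule, so there is no figure of its own to reproduce. The four regression sample sizes (288, 344, 680, 459) are not in question.

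**Assumptions.** KL is computed on histograms of predicted risk. Predictors are independent, with assumed prevalences. Because the article fixes no estimator, a range of bin counts is shown.

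**Step 1: expected KL from sampling error alone.** For k evenly filled bins, E[KL] ≈ (k − 1)/2 × (1/691 + 1/2072) = (k − 1)/2 × 0.00193.
- k = 10: 4.5 × 0.00193 = 0.009
- k = 20: 9.5 × 0.00193 = 0.018
- k = 50: 24.5 × 0.00193 = 0.047

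The expected value passes 0.01 at k = 1 + 0.02/0.00193, about 11 bins. It reaches 0.1 at k = 1 + 0.2/0.00193, about 105 bins. Neither depends on the model.

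**Step 2: noise against signal at 2072/691.** Class-weighted XGBoost, 10% events, 60 replicates per row, mean KL by binning:

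| Model | Outcome | Train AUC | Test AUC | 10 equal-width | 10 quantile | 20 quantile | 50 equal-width |
|---|---|---|---|---|---|---|---|
| Default | noise | 0.65 | 0.50 | 0.0072 | 0.0084 | 0.0177 | 0.0334 |
| Default | signal | 0.72 | 0.65 | 0.0085 | 0.0088 | 0.0178 | 0.0364 |
| Most complex | noise | 0.73 | 0.51 | 0.0105 | 0.0100 | 0.0199 | 0.0406 |
| Most complex | signal | 0.78 | 0.60 | 0.0093 | 0.0089 | 0.0178 | 0.0393 |

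KL moves with the bin count. It barely moves with whether the model predicts anything, and it does not flag the training–test gaps on noise (0.15 and 0.22). A separate simulation with a saturated model (one risk per pattern) and 10 quantile bins agrees: mean KL was 0.009 on noise (training AUC 0.73, test 0.50) and 0.009 on signal (0.77 and 0.58).

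**Step 3: the bands on noise at 2072/691.** Across ridge logistic regression, XGBoost and the saturated model, KL was below 0.1 in 100% of runs. The share below 0.01 was 45–100% with 10 bins, 0–34% with 20 and 0–6% with 50. A further XGBoost noise simulation, with equal-width bins and 0.5 added per bin, gave 97%, 77% and 28% below 0.01 for 5, 10 and 20 bins (5% events, depth 3).

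**Step 4: does KL respond to sample size?** For a 75/25 split and 10 bins, the formula becomes 4.5 × (1/0.25N + 1/0.75N) = 24/N, that is 0.035 at N = 680, 0.08 at N = 300 and 0.24 at N = 100. Simulation with real signal, 10% events, no class weights and 10 quantile bins:

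| Total N | Model | Train AUC | Test AUC | Mean KL | Runs below 0.1 |
|---|---|---|---|---|---|
| 300 | Ridge LR | 0.73 | 0.63 | 0.0787 | 76% |
| 300 | Most complex XGBoost | 0.93 | 0.61 | 0.0732 | 80% |
| 680 | Ridge LR | 0.70 | 0.65 | 0.0354 | 100% |
| 680 | Most complex XGBoost | 0.87 | 0.57 | 0.0364 | 100% |

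KL rises as N falls, as sampling error predicts. At a given N it is about the same for a model with a small training–test gap (0.05 at N = 680) as for one with a large gap (0.30).

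**The case against.** A reader might infer that a worthless model always passes the rule, that KL cannot respond to a small sample, and that adequacy would be concluded whatever the data show. The article supports none of these.

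- It sets descriptive bands, not a pass line. The 100% figure applies to the 0.1 boundary at this sample size only; the share below 0.01 on noise varies widely.
- KL does respond to sample size. With a total of 100, noise fits of logistic regression and XGBoost exceeded 0.1 in 10–75% of runs with 10 equal-width bins and in 50–92% with 10 quantile bins. This is sampling noise and not predictive failure, but it is a response.
- KL is offered as corroboration beside performance-based learning curves on non-AF and AF data, and 2.7 itself calls post hoc power analysis substandard. No model or CPR choice is tied to the KL value. Held-out AUC with CIs, training–test differences and calibration slopes are all to be reported, and would expose a useless model.

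It is also fair to say that pure noise is not the same thing as too small a sample for a real signal. The signal runs in steps 2 and 4 answer that: KL stays blind to overfitting there too.

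All this limits the harm but does not rescue the inference. Section 2.7's admission concerns weak evidence, whereas this check does not bear on the question. Section 2.7 also describes the learning curves for ML models while applying KL explicitly to ML and DL, although Table 4 names both checks for the MLP.

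**Conclusion.** Wrong as written, with a limited effect. At 2072/691 a small KL does not support the conclusion that the models generalise or that the sample is adequate. Mean KL was practically the same for a noise model as for a model with signal (0.0084 against 0.0088), noise never reached the top band, and whether KL falls below 0.01 depends heavily on a binning choice the article does not make. The damage is one unsupported corroborating inference; no planned performance result depends on it.

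This rests on histogram-based KL of predicted risks, the eight listed predictors as the only model inputs, and assumed, independent predictor prevalences. If continuous inputs also entered the models, training and test predictions could separate under overfitting and the result would need rechecking. The MLP was not simulated; for it the conclusion rests on the structural argument that any model is a function of the same 192 patterns at most.

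**What to change.** - In 2.7, remove the statements that KL assesses generalisation capability and that a small KL corroborates sample-size adequacy.
- Remove KL from the sampling-plan cells of Tables 3 and 4, or keep it only as a description of how balanced the split is, with the estimator and binning named.
- Judge adequacy for XGBoost and the MLP by quantities that use outcomes: the training-minus-test difference in AUC, already planned under Model Evaluation, with log loss added (it is already the inner-loop selection metric); the calibration slope on the test set, already planned, with a CI added; and the AF-specific learning curves in 2.7, extended explicitly to the MLP so that 2.7 matches Table 4.

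The cost is rewording one section and two table cells, plus negligible analysis work.
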